## Abstract

**Background:**

Strong evidence exists that substance use is a contributory risk factor for intimate partner abuse (IPA) perpetration. Men in substance use treatment are more likely to perpetrate IPA than men from the general population. Despite this, referral pathways are lacking for this group. This trial will assess the feasibility of conducting an evaluation trial of a tailored integrated intervention to address substance use and IPA perpetration to men in substance use treatment.

**Methods/design:**

ADVANCE is a multicentre, parallel-group individually randomised controlled feasibility trial, with a nested formative evaluation, comparing an integrated intervention to reduce IPA + substance use treatment as usual (TAU) to TAU only. One hundred and eight men who have perpetrated IPA in the past 12 months from community substance use treatment in London, the West Midlands, and the South West will be recruited. ADVANCE is a manualised intervention comprising 2–4 individual sessions (2 compulsory) with a keyworker to set goals, develop a personal safety plan and increase motivation and readiness, followed by a 12-session weekly group intervention delivered in substance use services. Men will be randomly allocated (ratio 1:1) to receive the ADVANCE intervention + TAU or TAU only. Men’s female (ex) partners will be invited to provide outcome data and offered support from integrated safety services (ISS). Regular case management meetings between substance use and ISS will manage risk. Outcome measures will be obtained at the end of the intervention (approximately 4 months post-randomisation) for all male and female participants. The main objective of this feasibility trial is to estimate parameters required for planning a definitive trial including rates of consent, recruitment, and follow-up by site and group allocation. Nested formative evaluation including focus groups and in-depth interviews will explore the intervention’s acceptability to participants, group facilitators, keyworkers and ISS workers. Secondary outcomes include substance use, IPA, mental health, self-management, health and social care service use, criminal justice contacts, and quality of life.

**Discussion:**

Findings from this feasibility trial will inform the design of a multicentre randomised controlled trial evaluating the efficacy and cost-effectiveness of the ADVANCE intervention for reducing IPA and improving the well-being of female (ex)partners.

**Trial registration:**

ISRCTN79435190.

## Background

Intimate partner abuse (IPA) includes any incident/pattern of incidents of controlling, coercive or threatening behaviour, violence, or abuse between current or former partners [1]. Women are more likely to experience sexual violence, injury, or be murdered by a partner than men [2–5]. While no single factor explains why some people perpetrate IPA [6, 7], there is strong and consistent evidence that substances, particularly alcohol, cocaine, and methamphetamines are contributory risk factors for IPA perpetration [8–16]. This association is significantly stronger from men who abuse or are dependent on alcohol or drugs [16]. The complex interplay between substance use and IPA perpetration includes intoxication (change or disinhibition when under the influence of alcohol or stimulant drugs), withdrawal and craving (irritability and frustration or the need to acquire substances), the impact of substance use on relationships, the wider dynamics of power and control, and psychological vulnerabilities (adverse childhood experiences, mental health, and emotional instability) linked to substance use and IPA [17, 18]. At least 3 in 10 men receiving substance use treatment have been physically or sexually violent, and 7 in 10 men have been psychologically abusive towards their partner in the previous year [3, 8, 9, 19–21]. These rates are far higher than amongst the general population [12, 14]. Around three-quarters of men attending substance use treatment in England had ever perpetrated any IPA towards their partner [9].

Despite the association between IPA perpetration and substance use, and the higher prevalence of IPA perpetration amongst men receiving substance use treatment, there is a lack of care pathways including perpetrator programmes for this client group [22]. Community perpetrator programmes in England (UK) meet only 10% of the existing demand [23]. Men who use substances are rarely referred to perpetrator programmes and when they are, treatment completion is low and attendance/uptake poor [24–27]. In one US study, only 17% of 658 men seeking alcohol treatment who had perpetrated IPA in the past year were referred to a perpetrator programme by the alcohol treatment service, and only 15 (13%) enrolled in the programme [27]. Amongst 286 males convicted for intimate partner violence and court-mandated to attend a community-perpetrator programme in Spain, a significantly higher rate of intervention drop-out was reported amongst men with alcohol problems (36% vs. 23%, *p* < .05) [26].

Few perpetrator interventions have been trialled amongst men who use substances [28]. A recent review of interventions to reduce IPA perpetration by men who use substances identified only nine trials, three of which were conducted in substance use treatment services and two of these amongst men who had been arrested for IPA or court-mandated to receive the intervention [28]. Initial reviews of IPA interventions conducted concurrently with alcohol treatment [29] or integrated interventions that address both IPA and substance use [28] show some promise but were not superior to treatment as usual [28]. Some interventions to address IPA in men who use substances present a simplistic model of inebriated physical violence and struggle to integrate issues of gender, non-physical abuse and to fully consider the impact of a substance use lifestyle. Recent research has identified that it is not one factor that explains causal pathways into IPA, but rather a multilevel and multifactor explanation is required [17, 18, 30]. A nested ecological model identifies factors at 4 levels, including structural factors such as patriarchy, sub-cultural factors, for example, high tolerance for general alcohol use, familial factors, including modelling from family of origin and social learning theory, and individual factors such as high anger or high impulsivity [31]. This multifactorial response requires a more nuanced understanding of the roles of substance use in IPA perpetration that is wider than intoxicated abuse. Withdrawal and craving present as many risks as intoxication and intensify coercive control [18]. Many perpetrators report psychological problems and explain IPA as a shared response to anxiety or depression and anger, often from emotional insecurities shaped by negative childhood experiences, and mediated by substances [17].

## Rationale

IPA is not routinely identified or addressed in substance use treatment, resulting in a large proportion of perpetrators who might benefit from treatment being missed. Ultimately, training substance use treatment staff to deliver integrated interventions to address IPA in substance use treatment services would increase their reach.

We are not aware of any UK-based randomised control trials of the effectiveness of perpetrator programmes for men who use substances. Further research is needed to develop and test integrated interventions that address IPA and substance use concurrently. The provision of strategies to holistically address both may be more effective [32].

## Methods

The protocol (Version 5, 13 November 2018) complies with the guidelines of the Standard Protocol Items: Recommendations for Interventional Trials (SPIRIT) [33] (Table 1).

**Table 1 Tab1:** SPIRIT Checklist

Section/item	Item no.	Description	Addressed on page number
Administrative information			
Title	1	Descriptive title identifying the study design, population, interventions, and, if applicable, trial acronym	Title page
Trial registration	2a	Trial identifier and registry name. If not yet registered, name of the intended registry	Abstract, 2
Protocol version	3	Date and version identifier	3
Funding	4	Sources and types of financial, material, and other support	15
Roles and responsibilities	5a	Names, affiliations, and roles of protocol contributors	15
	5b	Name and contact information for the trial sponsor	15
	5c	Role of study sponsor and funders, if any, in study design; collection, management, analysis, and interpretation of data; writing of the report; and the decision to submit the report for publication, including whether they will have ultimate authority over any of these activities	15
	5d	Composition, roles, and responsibilities of the coordinating centre, steering committee, endpoint adjudication committee, data management team, and other individuals or groups overseeing the trial, if applicable (see Item 21a for data monitoring committee)	14
Introduction			
Background and rationale	6a	Description of research question and justification for undertaking the trial, including summary of relevant studies (published and unpublished) examining benefits and harms for each intervention	2–3
	6b	Explanation for choice of comparators	10
Objectives	7	Specific objectives or hypotheses	3, 10–11
Trial design	8	Description of trial design including type of trial (e.g. parallel group, crossover, factorial, single group), allocation ratio, and framework (e.g. superiority, equivalence, noninferiority, exploratory)	3
Methods: participants, interventions, and outcomes			
Study setting	9	Description of study settings (e.g. community clinic, academic hospital) and list of countries where data will be collected. Reference to where list of study sites can be obtained	3
Eligibility criteria	10	Inclusion and exclusion criteria for participants. If applicable, eligibility criteria for study centres and individuals who will perform the interventions (e.g. surgeons, psychotherapists)	3, 6
Interventions	11a	Interventions for each group with sufficient detail to allow replication, including how and when they will be administered	9–10
	11b	Criteria for discontinuing or modifying allocated interventions for a given trial participant (e.g. drug dose change in response to harms, participant request, or improving/worsening disease)	13
	11c	Strategies to improve adherence to intervention protocols, and any procedures for monitoring adherence (e.g. drug tablet return, laboratory tests)	10
	11d	Relevant concomitant care and interventions that are permitted or prohibited during the trial	10
Outcomes	12	Primary, secondary, and other outcomes, including the specific measurement variable (e.g. systolic blood pressure), analysis metric (e.g. change from baseline, final value, time to event), method of aggregation (e.g. median, proportion), and time point for each outcome. Explanation of the clinical relevance of chosen efficacy and harm outcomes is strongly recommended	11–13
Participant timeline	13	Time schedule of enrolment, interventions (including any run-ins and washouts), assessments, and visits for participants. A schematic diagram is highly recommended (see figure)	Fig. 1, Table 2, 6–8
Sample size	14	Estimated number of participants needed to achieve study objectives and how it was determined, including clinical and statistical assumptions supporting any sample size calculations	13–14
Recruitment	15	Strategies for achieving adequate participant enrolment to reach target sample size	10
Methods: assignment of interventions (for controlled trials)			
Allocation:			
Sequence generation	16a	Method of generating the allocation sequence (e.g. computer-generated random numbers), and list of any factors for stratification. To reduce predictability of a random sequence, details of any planned restriction (e.g. blocking) should be provided in a separate document that is unavailable to those who enrol participants or assign interventions	8
Allocation concealment mechanism	16b	Mechanism of implementing the allocation sequence (e.g. central telephone; sequentially numbered, opaque, sealed envelopes), describing any steps to conceal the sequence until interventions are assigned	8
Implementation	16c	Who will generate the allocation sequence, who will enrol participants, and who will assign participants to interventions	8
Blinding (masking)	17a	Who will be blinded after assignment to interventions (e.g. trial participants, care providers, outcome assessors, data analysts), and how	8
	17b	If blinded, circumstances under which unblinding is permissible, and procedure for revealing a participant’s allocated intervention during the trial	8
Methods: data collection, management, and analysis			
Data collection methods	18a	Plans for assessment and collection of outcome, baseline, and other trial data, including any related processes to promote data quality (e.g. duplicate measurements, training of assessors) and a description of study instruments (e.g. questionnaires, laboratory tests) along with their reliability and validity, if known. Reference to where data collection forms can be found, if not in the protocol	11–13
	18b	Plans to promote participant retention and complete follow-up, including a list of any outcome data to be collected for participants who discontinue or deviate from intervention protocols	10
Data management	19	Plans for data entry, coding, security, and storage, including any related processes to promote data quality (e.g. double data entry; range checks for data values). Reference to where details of data management procedures can be found, if not in the protocol	11–13
Statistical methods	20a	Statistical methods for analysing primary and secondary outcomes. Reference to where other details of the statistical analysis plan can be found, if not in the protocol	14
	20b	Methods for any additional analyses (e.g. subgroup and adjusted analyses)	14
	20c	Definition of analysis population relating to protocol non-adherence (e.g. as randomised analysis), and any statistical methods to handle missing data (e.g. multiple imputation)	14
Methods: monitoring			
Data monitoring	21a	Composition of data monitoring committee (DMC); summary of its role and reporting structure; statement of whether it is independent from the sponsor and competing interests; and reference to where further details about its charter can be found, if not in the protocol. Alternatively, an explanation of why a DMC is not needed	13–14
	21b	Description of any interim analyses and stopping guidelines, including who will have access to these interim results and make the final decision to terminate the trial	13
Harms	22	Plans for collecting, assessing, reporting, and managing solicited and spontaneously reported adverse events and other unintended effects of trial interventions or trial conduct	13
Auditing	23	Frequency and procedures for auditing trial conduct, if any, and whether the process will be independent from investigators and the sponsor	13
Ethics and dissemination			
Research ethics approval	24	Plans for seeking research ethics committee/institutional review board (REC/IRB) approval	15
Protocol amendments	25	Plans for communicating important protocol modifications (e.g. changes to eligibility criteria, outcomes, analyses) to relevant parties (e.g. investigators, REC/IRBs, trial participants, trial registries, journals, regulators)	15
Consent or assent	26a	Who will obtain informed consent or assent from potential trial participants or authorised surrogates, and how (see Item 32)	6-8
Confidentiality	27	How personal information about potential and enrolled participants will be collected, shared, and maintained in order to protect confidentiality before, during, and after the trial	14
Declaration of interests	28	Financial and other competing interests for principal investigators for the overall trial and each study site	15

### Aim

This trial will assess the feasibility of conducting an evaluation trial of an integrated intervention to address both substance use and IPA perpetration to men in substance use treatment.

### Design

A multicentre, parallel group, individually randomised controlled feasibility trial with a nested formative evaluation, comparing an integrated intervention to reduce IPA + usual substance use treatment, to usual substance use treatment only for men in substance use treatment.

### Setting and participants

One hundred and eight male participants will be recruited from NHS and voluntary organisation community substance use treatment services in three regions in England (two services in London, two services in the West Midlands and two services in the South West). Sets of up to 18 men per treatment service will be randomised. Three sets of the 16-week ADVANCE intervention, one in each region, will be completed (cycle 1) and a formative evaluation undertaken to inform the implementation of cycle 2 (a further three sets of the intervention, one in each region). Up to 18 men per set will randomised per cycle.

The female current or former partners of men recruited to the trial will be offered support from an integrated safety service and invited to provide outcome data for the trial. Based on recruitment figures from other evaluations of perpetrator programs [34] and a recent UK-based perpetrator intervention [35], it is estimated that up to 70% of their current or former female partners will be recruited (*n* = 76).

### Inclusion and exclusion criteria

Men attending the substance use treatment services are eligible if:
They have perpetrated IPA towards a current or ex female partner in the last 12 monthsHave had face-to-face/phone/text/social media contact at least once with that partner in the last 12 monthsPlan to stay in the current location for the next 6 monthsAgree to provide contact details of current and/or ex female partnerAble to understand and communicate in English

Men will be excluded if any of the following apply:
Current restraining orders prohibiting them or anyone on their behalf (e.g. the women’s support worker or the researcher) from contacting their current or ex female partnerPending court cases for IPA as it is uncertain how they will be sentenced (i.e. they may not be able to participate in the trial)Pending child protection hearings to ensure that participating in the trial could not be used to influence proceedingsAttending an intervention for IPA perpetration

For eligible men following the screening, the keyworker at the substance use treatment service will assess men’s suitability to participate in the trial.

For women whose current or former partners are participating in the trial, inclusion criteria include
Being aged 18 years or olderAn ability to understand and communicate in English

Women will be excluded if any of the following apply:
Pending court cases for IPAPending child protection hearings

In exceptional circumstances, clinicians can override the inclusion criteria to ensure that female current or former partners are safeguarded including (1) where the female and male participant share a mobile phone and (2) where the female partner lives outside the UK and therefore integrated safety support cannot be provided—neither will be eligible to take part in the feasibility trial.

Male current or former partners and non-English speaking female current or former partners of men in the trial will not be invited to provide outcome data but will be offered support for their IPA victimisation.

### Recruitment

Participation in the trial requires a two-stage informed consent process. Firstly, men must consent to be screened for eligibility. If eligible after screening, men then consent to take part in the trial. Researchers will screen potential male participants for eligibility using the Revised Abusive Behavior Inventory [36]. Men already attending substance use treatment will be identified in substance use treatment waiting rooms, via keyworkers or will contact researchers from details on flyers/posters advertising the research (Fig. 1). Researchers will also attend support groups delivered in the substance use service to explain the study and invite interested men to discuss the study further. Men who report this is their first appointment at the service will not be screened as they may not be enrolled in the service following assessment. To be eligible to participate in the trial, male participants have to be receiving treatment from the participating substance use service.

**Fig. 1 Fig1:**
[figure not shown]
Flow of participants through the trial

Researchers will explain the study to interested men, provide them with an information sheet and gain informed consent to undertake the screening, including limitations to confidentiality and consent to discuss the screening and their suitability to take part in the trial with their keyworker. Consent forms will be counter-signed in triplicate by both the male participant and the researcher. Male participants will receive a copy of the signed consent form; a copy will be filed in the Investigator Site File and a copy will be attached to the letter to the male participant’s keyworker at the substance use treatment service. This letter will inform the keyworker that their client has screened positive for past year IPA and identify areas of risk (e.g. threat/use of a weapon against partner or choking/strangulation of partner) for potential further assessment by the keyworker. It will also include the name of their client’s current and/or former female partner. Keyworkers then are able to consider the suitability of their client to participate in the trial (e.g. cognitive deficit or mental health problems that may limit their ability to participate).

If eligible, following screening and their keyworkers deem the participant suitable to take part, male participants will complete a baseline assessment administered by the researcher (see Section 3.14). The researcher will again explain the study to eligible men, provide them with an information sheet and get their informed consent to participate in the trial prior to administering the baseline questionnaire. In addition, men will complete a consent quiz [37] to ensure they understand the trial procedures. Researchers will clarify any incorrect responses with the participant. Men will be randomised to treatment conditions following baseline assessment. Their keyworkers will be informed of which group they have been allocated to by a letter from the researcher. All interviews with men will be conducted in a private room of the substance use treatment service.

Following baseline assessment and randomisation of male participants, their current or former female partners will be contacted by telephone by an integrated safety service worker to (1) inform them their current or former partner is participating in the trial; (2) to offer them support for IPA victimisation; and (3) invite them to participate in the research by providing outcome data. Women can accept the offer of support without participating in the research and vice-versa. If women are interested in participating in the research, their contact details will be passed to the research team, who will contact them within 1 week and arrange a time for an initial interview to be conducted with the researcher (see Section 3.14). At this meeting, the researcher will explain the trial to the woman and gain informed consent prior to administering the baseline interview. Women will be interviewed in a women’s support service, a substance use treatment service, a children’s centre, or in exceptional cases, it may be possible for two researchers to interview the women in her home.

After each interview, male and female participants will be given contacts for local and national helplines and services. If specific risk issues are identified within the baseline assessment, appropriate steps will be taken to manage this risk, including disclosure to the participant’s keyworker (for male participants), and/or to the integrated safety worker (for women participants).

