**Fig. 2 Fig2:**
[figure not shown]
ADVANCE intervention

Pre-group individual sessions will be delivered by keyworkers in substance use treatment service. The group intervention will also be delivered in substance use treatment services by two trained facilitators, where possible one female and one male. Keyworkers or facilitators will check-in by phone with participants between group sessions to address any issues arising during the session. Participants will be given out of session practice exercises. Facilitators will send a weekly feedback to participants’ keyworkers by email after each session to update them on progress, safeguarding issues and risk. Group sessions will be video recorded with participants’ consent and checked for fidelity. Only those consenting to being video recorded would be able to take part in the trial.

Fortnightly, integrity support meetings will be held with facilitators to discuss delivery issues and address any expected problems for delivery of the next two sessions. Four case management meetings will take place with facilitators (and keyworkers where possible) and the integrated safety service workers over the course of the intervention to consider risk. Aftercare is provided in the form of workbooks for men, keyworker guidance, and signposting.

Contingency management, recommended by the National Institute for Health and Care Excellence [43], will be used to encourage motivation and retention of participants in the group intervention by offering incentives to attend the ADVANCE integrated intervention. Participants in the intervention arm only will receive a £5 voucher (for a shop or service of their choosing) for attending each of the 12 sessions up to a total of £60. These will be awarded at session 6 and session 12 of the group intervention. If a participant attends all 12 sessions an additional £10 ‘bonus’ voucher will be available. Travel will also be reimbursed, and refreshments provided.

The integrated safety service will also contact the female current or former partners of males in the intervention arm on at least three occasions to update them on their current or ex-partner’s overall progress within the intervention. They will also contact women if there is anything that they need to know to keep themselves and their families safe.

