### Participant-centred outcome measures

The suitability and acceptability of outcome measures will be assessed to determine the feasibility of including them in a future effectiveness trial. Researchers’ perceptions of participants’ understanding (e.g. of language and meaning of questions) and acceptability (e.g. if participant refuses to answer or gets annoyed/frustrated or asks to end the interview) will be recorded for each outcome measure using a pre-determined rating scale (1—lowest rating to 3—highest rating for understanding and acceptability). The following outcome measures will be assessed at baseline for men and initial interview for women and at the end of the intervention (4 months post-randomisation of men) for men in both treatment arms and their current or former female partners (unless otherwise specified) (Table 2).

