### Intimate partner abuse (victimisation and perpetration) in the past 4 months

*The Abusive Behaviour Inventory Revised* (ABI-R) is a 25-item reliable tool to measure experiences of physical (13 items), psychological (9 items), and sexual abuse (3 items) victimisation and perpetration [36]. Each item can be scored from 1 (never) to 5 (very frequently). The higher the score on each subscale, the greater the frequency of abuse.

Controlling behaviours in relation to both perpetration and victimisation will be assessed using four adapted questions from the 24 item *Revised Controlling Behaviours Scale* (CBS-R) [53]: smash your partner’s property when annoyed/angry; want to know where your partner went and who they spoke to when not together; tell your partner they were going mad; and try to restrict time your partner spent with family or friends. Total score for the 4 questions ranges from 0 to 16; the higher the score, the greater the frequency of a partner using controlling behaviours.

*The Communications Patterns Questionnaire-Short Form* (CPQ-SF) [54] is an 11-item self-assessment of “spouses’ perceptions of marital interactions … to indicate the representativeness of that description for the conflict and communication patterns in their relationship”: male demand/female withdraw; female demand/male withdraw; original total demand/withdraw; alternate demand/withdraw; criticise/defend and positive interaction. Higher scores on each subscale suggest which communication pattern is likely to be used during conflict interactions.

Two scales (9 items) from *The Intimate Partner Violence Responsibility Attribution Scale* (IPVRAS) (included in the male baseline and follow-up questionnaires only) will assess perpetrators’ responsibility attribution to the victim (V) and responsibility attribution to the offender’s (i.e. perpetrator’s) personal context (O) [55]. The higher the score, the more responsibility attributed to the victim (V) or offender’s personal context (O).

The 12-item anger subscale from *The Propensity for Abusiveness Scale* (PAS) (included in the male baseline and follow-up questionnaires only) is included. The PAS predicts the perpetration of physical and emotional abuse. Scores on the anger subscale range from 12 (completely undescriptive of you) to 60 (completely descriptive of you) [56].

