#### Statistical analysis

This feasibility trial will estimate parameters needed for planning an efficacy trial including estimating various rates (e.g. recruitment, randomisation, follow-rates) and estimating the within-trial arm standard deviation, the pre-post correlation, and the Intracluster Correlation Coefficient (*ICC*) for possible outcome measures to inform the sample size calculation of a future randomised control trial. Outcome measures will be rated by the researcher for each participant for their suitability and acceptability and the mean scores summarised for each outcome. Outcome measures will be described by trial arm. Intervention effect sizes (e.g. incidence rate ratios for the count outcome and mean differences for continuous outcome measures) will be estimated for various outcome measures, but no formal hypotheses testing will be carried out.

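### Women's baseline interviews come after the man's randomisation, so their 4-month abuse recall overlaps the follow-up and the women's pre-post correlation is biased upward

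*Protocol article*

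**What the plan says.** The Recruitment section sets the order. Men consent, complete their baseline and are randomised. Then: "Following baseline assessment and randomisation of male participants, their current or former female partners will be contacted by telephone". The caller is a safety-service worker, who tells the woman that the man has joined the trial. The same call offers support and invites the woman to the research. Interested women are then referred on to researchers, "who will contact them within 1 week and arrange a time for an initial interview to be conducted with the researcher". When they meet, "the researcher will explain the trial to the woman and gain informed consent prior to administering the baseline interview". The only interval with a limit is the researchers' call. Neither the first safety-service call nor the interview itself has a time limit.

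The Blinding section says that researchers know the allocation. The section Participant-centred outcome measures places the second assessment "at the end of the intervention (4 months post-randomisation of men", so the woman's follow-up is counted from his randomisation and not from her own first interview. The abuse measures stand under the heading "Intimate partner abuse (victimisation and perpetration) in the past 4 months". The Statistical analysis section lists "the pre-post correlation" among the quantities to be estimated for the sample size of the future trial. Table 2 has one column for baseline and randomisation together and does not show that women come later than men.

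**The concern.** A pre-post correlation is useful for planning if the first measurement precedes allocation and the two measurements cover separate periods. For women and the 4-month abuse measures, neither is secured. Part of the time recalled at her baseline lies after the man's randomisation, and the same time is recalled again at follow-up. By then she has been told that he is in the trial and offered safety-service support, which is available in both arms. In the intervention arm his individual sessions may also have begun.

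Two planning quantities suffer. The correlation is pushed up by the shared recall. A sample size for a trial with a true baseline that relies on it would be too small. A baseline that already contains part of any effect also shrinks a change-score or baseline-adjusted estimate. Separately, women's uptake by arm is uptake after allocation, obtained in part by staff who know the arm, and should be read as such.

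**Working it through.** **The plan's own figures.** Sample size calculation section: 60 women at follow-up, 80% retention, 70% uptake. 60/0.80 = 75 (stated 76). 76/0.70 = 108.6 (stated as approximately 108). Forwards: 108 × 0.70 = 75.6, and 75.6 × 0.80 = 60.5. The figures reproduce within rounding, and none depends on when the woman's baseline is taken.

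**Overlap.** Let the man's randomisation be time 0 and the woman's baseline take place t months later. Her baseline recall covers (t - 4, t) and her follow-up recall covers (0, 4). For t between 0 and 4 the shared time is t months, a share t/4 of each window. If follow-up slips s months past 4, the overlap is t - s, or zero if s is at least t.

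**Lag.** The documents do not give t, so it is an assumption. With 4 months = 17.4 weeks, 1 week is 0.23 month and 2 weeks is 0.46 month.

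**Correlation.** Assume that a 4-month score acts like the sum of four monthly scores with equal variance and a common between-month correlation ρ, taken as 0.2 to 0.5.

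- No overlap: r = 16ρ / (4 + 12ρ). For ρ = 0.2 this is 3.2/6.4 = 0.50. For ρ = 0.5 it is 8/10 = 0.80.
- Overlap t: r = (16ρ + t(1 - ρ)) / (4 + 12ρ). For ρ = 0.2, r = 0.50 + 0.125t. For ρ = 0.5, r = 0.80 + 0.05t. Parts of a month are interpolated linearly.

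The variance factor for an analysis adjusted for baseline is 1 - r². Without overlap it is 0.75 (ρ = 0.2) or 0.36 (ρ = 0.5).

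| Assumed lag | Share of recall window | r, ρ = 0.2 | Fall in 1 - r² | r, ρ = 0.5 | Fall in 1 - r² |
|---|---|---|---|---|---|
| 1 week | 6% | 0.53 | 4% | 0.81 | 5% |
| 2 weeks | 11% | 0.56 | 8% | 0.82 | 10% |
| 1 month | 25% | 0.625 | 19% | 0.85 | 23% |

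Example, 1 month and ρ = 0.2: 1 - 0.625² = 0.609, and 0.609/0.75 = 0.81, a fall of 19%.

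**Dilution.** Assume that any effect is uniform over the follow-up window. A change score keeps 1 - t/4 of it: 94% at 1 week, 89% at 2 weeks (0.885), 75% at 1 month. With baseline adjustment at an assumed slope of 0.5 it keeps 1 - 0.5t/4: 97%, 94% and 88% (0.875).

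**What is outside the overlap.** The follow-up standard deviation uses one window only. Scales with 2-week or 4-week recall overlap little or not at all. Men's baselines precede their randomisation.

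**The case against.** The strongest reply is that this is a feasibility trial with no formal hypothesis testing. Uptake by arm is itself a feasibility measure, so unequal uptake after allocation would be revealed rather than hidden, and the order could be changed for the definitive trial. This stands, and it lowers the urgency. It does not help the correlation, which the trial means to carry forward.

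The size may also be small. The only stated interval is 1 week for the researchers' call. At a lag of 1 to 2 weeks r moves by about 0.01 to 0.06, whereas with 60 pairs the 95% interval around r = 0.50 is about 0.28 to 0.67 (Fisher z, standard error 1/√57). The abuse items are single frequency ratings and not monthly counts, so the model is only a guide. Follow-up is at approximately 4 months, and slippage would shrink the overlap. All of this stands. But the bias runs in one direction and is cheap to avoid, and nothing in the article limits the lag to 2 weeks.

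A reader might infer three stronger things that the document does not support.

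- **The safety worker who makes the first call knows the allocation.** Only researchers are stated to be unblinded. For the safety worker at that call it is an inference.
- **Extra contact in the intervention arm distorts women's recruitment.** The safety service will "contact the female current or former partners of males in the intervention arm on at least three occasions", but these are progress updates. Nothing ties them to research recruitment, and they would continue wherever the woman's baseline was placed.
- **The definitive trial will be undersized by nearly half.** A 42-47% fall in 1 - r² needs a 2-month lag (r = 0.75 or 0.90), which the article does not state. It also needs a definitive trial that adjusts a woman-reported abuse scale for a true pre-randomisation baseline, which the article does not fix.

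**Conclusion.** The point holds in a limited form. The order of events and the unblinded interviewers are explicit, and the overlap follows from the article's own 4-month recall and 4-month follow-up. As planned, the women's correlation on the 4-month abuse measures is not a true pre-post figure and errs upward. The understatement of 1 - r² is about 4-5%, 8-10% and 19-23% at lags of 1 week, 2 weeks and 1 month. These figures rest on an assumed lag, an exchangeable monthly model and follow-up at exactly 4 months. The dilution of change-score or adjusted effects rests also on an effect spread evenly over the follow-up window. If the definitive trial repeated the same lag, the correlation would carry over, but the dilution would remain.

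It would be wrong to conclude that the sample size is unsound: its justification is the estimation of a standard deviation, and the follow-up standard deviation has no overlap. This is a low-cost improvement to a planning parameter and does not put the trial as a whole in doubt.

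**What to change.** 1. Record the days from the man's allocation to each woman's first interview, and label that interview as post-randomisation in the analysis and in Table 2.
2. For the 4-month abuse measures, do one of two things. Either word the woman's baseline recall to end on the man's randomisation date, which makes the overlap zero, or leave overlapping baselines out of the women's pre-post correlation and out of any baseline adjustment. The first option does not remove any influence of allocation or support on how she reports, so the label in step 1 is still needed.
3. Report women's uptake by arm as post-allocation uptake.

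The cost is one extra date field, and either slightly fewer pairs or a slightly more distant recall period. The sample size does not change.

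Inviting women before the allocation is released would remove the problem at its source. It would also split a call that now combines information, support and the research invitation, and it would delay allocation. It is an option to weigh with the safety service, for this trial or the definitive one, and not a required change.
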